### Baseline and outcome measures

Outcome measures will be collected at four time points: pre-, mid-, post-intervention and 3-month follow-up (see Fig. 1 and the SPIRIT checklist [35] in Supplementary Material). The measures will be administered by the research therapist using telecommunication methods including video conferencing technology to direct the caregiver to manipulate materials appropriately. The measures can be successfully administered with non-verbal and minimally verbal children and can ultimately be easily integrated in clinical and research settings. They will be scored by the research therapist and checked by a research assistant who will be blind to allocation. However, the parent administering the measures will also have been using the intervention methods with their children and thus there is very limited blinding possible in this trial. Demographic details and a medical history will be obtained at intake to the trial. Given the small size of this randomised controlled feasibility trial, there is no need to define primary versus secondary outcomes [24]. Thus, the following outcome measures are listed with no particular order.One key outcome is the expressive (picture naming) and receptive (pointing to correct picture) tasks to assess the production and comprehension of the 36 target words at baseline, post-intervention, and 3-month follow-up. A preliminary list of 36 target words has been drawn up (Table 1), but the protocol includes 35 backup words (Table 2) and allows substitutions of up to 10 words if required by the prior skills of the child;Social Responsiveness Scale-2 (SRS-2) - Participants’ ASD symptomatology will be assessed using the Social Responsiveness Scale-2 [29]. The SRS-2 is a questionnaire that uses a scale of 1–4 (1 = not true, 4 = almost always true) to rate items, with higher scores indicating greater impairment [36, 37]. A designated raw score cutoff value of 70 is considered to have a sensitivity of 0.78 and specificity of 0.94 for ASD [38]. Raw total scores are converted to gender-normed T scores, with a T score of 75 indicating severe impairment. Item-level and full scale (both raw and T scores) scores were included in the analyses.Receptive and expressive language skills will be measured using the Expressive One-Word Picture Vocabulary Test–4 (EOWPVT-4) [39] and the Receptive One-Word Picture Vocabulary Test-4 (ROWPVT-4) [40], and by MacArthur Bates Communicative Development Inventories (CDI): Words and Gestures Forms [41]. The EOWPVT-4 and ROWPVT-4 tests give raw score which can be used to determine standard score, age-equivalent score and percentile rank. The tests are appropriate for use with typical and atypical populations, including those with learning difficulties. The CDI has high parent-teacher agreement for children with ASD (intraclass correlation 95% CI estimates 0.77 to 0.93) [42].The child’s social communication will be evaluated during a 10-min video recorded free play session between the child and their parent. Social communication will be measured using the Parent-Child Dyadic Interaction Measure which has good intrarater (*κ* = .81) and good interrater reliability (*κ* = .80) [43].Functional language will also be evaluated during the 10-min video recorded free play session between the child and their parent. Casenhiser et al.’s (2015) [44] approach to coding language functions will be used which shows good internal consistency (Cronbach’s *α* range 0.830–0.836) as is the validity compared with other measures of communication level. A week-long language diary to be filled out by parents at pre-, mid-, post-intervention and 3-month follow-up will also help determine the child’s progress on language development.Communication, daily living skills, socialisation and maladaptive behaviour will be measured using the comprehensive parent/carer form of Vineland Adaptive Behavior Scales – Third Edition (VABS-3) [32], to be filled out by parents/caregivers. The VABS-3 has high internal consistency (Cronbach’s *α* range 0.86–0.97), good test-retest reliability (corrected *r* values range 0.62–0.92), and good inter-rater reliability (range 0.61 to 0.87). Data show that it has criterion validity for identifying those with intellectual disability.

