**Methods:**

In this protocol, we describe our music-assisted programmes (MAP) that will use music to attract the attention of people with ASD to speech. MAP may open the brain pathways to language and therefore help improve communication skills for people with ASD more than standard communication protocols. In particular, we aim to develop and test whether individualised, easily used MAP would increase spoken language in 24–60-month-old, nonverbal or minimally verbal children with ASD. We will develop a structured training method, delivered through naturalistic, interactive activities (e.g. songs) to teach language to ASD children. We will test this by comparing two groups: one undertaking music-assisted programmes, and the other receiving speech and language therapy in the way that is recommended in NHS clinics. Participants will be allocated to groups randomly. The feasibility of MAP will be assessed through estimations of recruitment and retention rates, the sensitivity and reliability of the outcome measures, the intensity and frequency of the trial, the usability of the MAP app (beta version), and the burden of the assessments for the children and parents.

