**Discussion:**

This feasibility randomised controlled trial will establish the acceptability and estimate the power of the MAP intervention to improve early word learning in children with ASD. In the longer term, this research will help us develop an app for parents or carers of children with ASD to design their own songs and implement their own individualised MAP.

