We will record and report the participant flow according to CONSORT guideline and produce a CONSORT flowchart [45, 46]. As a feasibility trial, we will report recruitment and retention figures for both MAP and TAU together with reasons for loss of participants. The trial management will consider any adverse effects and use that information to continue or halt the trial. In addition, we will discontinue the trial at the request of the caregivers, ongoing distress on the part of either the child or the caregiver, and if the caregiver takes up an additional language intervention during the trial. We expect to analyse recruitment and retention data using descriptive statistics involving both intention to treat and actual completed participant data. Recruitment and retention will be encouraged by payment of £202.50 ($283.00) to participants families for completing the research. The amount of the missing data will be recorded in order to assess the feasibility of using each measure. An important part of the feasibility is the extent to which it is possible to conduct two training sessions per week and still maximise the homework practice. We will therefore review the uptake/usage pattern of all MAP parent-child dyads to establish the feasibility of delivering 36 sessions over 18 weeks. For the outcome measures, descriptive data will include means and standard deviations for continuous normal data, and medians and inter-quartile ranges for continuous non-normal or discrete data. Standard errors/confidence intervals will also be calculated for continuous normal data or percentages. Statistical analyses will be performed in R [47]. The results from these analyses will provide data for effect size estimation. Together with the trial parameter data (i.e., recruitment, retention, follow-up and completion rate), these data will be used to determine the size of sample necessary to carry out a fully powered randomised controlled trial comparing MAP with SCIP. A preliminary categorical analysis of words learnt may be used to inform the selection of future vocabulary items for a subsequent trial. The numerical data will be analysed blind to allocation. The blinding will be carried out once the data are collected by generating a new series of participant codes, removing data that could lead to identification (TW) and then be analysed by the PI (FL). Anonymised behavioural data and statistical analysis codes will be made available following open access guidelines. The qualitative interview data will be transcribed and analysed using the thematic analysis framework [48] and Nvivo 12 [49].

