### Dissemination policies

The aim of dissemination will be to inform clinicians and parents of the potential usefulness or otherwise of the music-assisted programmes and the app that we are able to develop. This will be achieved through presentations to parent and voluntary groups. Other outputs will include conference presentations for organisations involved in the care and education of preschool children with ASD, and scientific conferences about interventions for ASD. A paper will be written for a peer-reviewed publication which we will make available cost free online.

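### The outcomes are left unranked, yet they are to supply the effect size and sample size of one full trial, and no outcome or time point is named for that purpose

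*Protocol article*

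**What the plan says.** Under Baseline and outcome measures, the protocol article argues from the trial's small size that "there is no need to define primary versus secondary outcomes", and adds that "the following outcome measures are listed with no particular order". The list contains ten measures: target words produced, target words understood, SRS-2, EOWPVT-4, ROWPVT-4, CDI, the dyadic interaction measure, functional language coding, the language diary and VABS-3. The two target-word tasks are together described as a key outcome, assessed at baseline, post-intervention and 3-month follow-up. For SRS-2 the text adds "Item-level and full scale (both raw and T scores) scores were included in the analyses".

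Objective 2, at the end of the Background, is to obtain parameter data for the sample size and effect size of a later full-scale trial. Data handling and analysis plan says that the outcome analyses will feed effect size estimation and that, with the recruitment, retention, follow-up and completion rates, "these data will be used to determine the size of sample necessary to carry out a fully powered randomised controlled trial comparing MAP with SCIP". The planned outcome analysis is descriptive: means and SDs or medians and quartiles, with standard errors or confidence intervals. It is to be done blind to allocation.

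The abstract's Methods section words the aim more strongly: "we aim to develop and test whether individualised, easily used MAP would increase spoken language". The abstract's Discussion says the trial will "establish the acceptability and estimate the power of the MAP intervention to improve early word learning".

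**The concern.** A feasibility trial does not need a primary efficacy outcome. The difficulty is that the article declines any ranking and then gives the same outcomes a task that requires a choice. A sample size calculation has to start from a specified outcome, or a specified set of outcomes, at specified times. Here none is specified, so the choice can be made once the between-arm differences are known.

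If the choice follows the result, the selected difference overstates the true one even when each single estimate is unbiased. The full trial would then be planned too small. This is separate from the imprecision of a single estimate from 30 children. Imprecision can err in either direction, whereas selection of the largest difference favouring MAP pushes upward.

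**Working it through.** **The plan's own figure.** The only precision statement is a drop-out rate of 20% estimated to within ±14% with 30 children. 1.96 × √(0.2 × 0.8 / 30) = 0.143, so it reproduces. It concerns retention and does not fix an outcome for sizing.

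**Does any section name the sizing outcome?**
- Background, objective 2: none named.
- Baseline and outcome measures: target words are called a key outcome, but this covers two tasks at two post-baseline visits and is not linked to sizing.
- Feasibility measures: the target-word measure may itself need revision.
- Data handling and analysis plan: effect size and sample size are mentioned, with no outcome or visit.

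**Inputs for the illustration.** From the article: 30 children, 20% drop-out, ten measures. Assumed: equal arms, so 30 × 0.8 / 2 = 12 completers per arm; outcomes standardised to SD 1; equal correlation of 0.5 between measures (range 0.3 to 0.8); a true effect of 0.3 SD on every measure; two-sided 5% level and 80% power for the full trial.

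**One outcome named in advance.** The standard error of the difference is √(2/12) = 0.408 SD, so the 95% half-width is 1.96 × 0.408 = 0.80 SD. The expected estimate equals the true 0.3 SD. The full-trial size is 2 × (1.96 + 0.84)² / 0.3² = 15.7 / 0.09, about 175 per arm.

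**Larger of the two target-word tasks, one visit.** The expected maximum is 0.3 + 0.408 × √((1 − r)/π).
- r = 0.5: 0.3 + 0.408 × 0.399 = 0.46 SD; 15.7 / 0.463² = about 73 per arm.
- r = 0.3: 0.49 SD, about 65 per arm.
- r = 0.8: 0.40 SD, about 97 per arm.

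**Best of all ten measures, one visit (worst case, simulated).**
- r = 0.5: median largest estimate 0.74 SD; 15.7 / 0.74² = about 29 per arm.
- r = 0.3: 0.82 SD, about 23 per arm.
- r = 0.8: 0.58 SD, about 47 per arm.

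**Power actually obtained if the true effect is 0.3 SD.** By the normal approximation, power is Φ(0.3 × √(n/2) − 1.96). For 73 per arm this is Φ(1.81 − 1.96), about 44%. For 29 per arm it is Φ(1.14 − 1.96), about 21%; the noncentral t gives about 20%.

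**The case against.** The strongest reply is that leaving out a primary outcome is a reasoned and referenced position for a small feasibility trial, and that none of the four objectives in the Background is a test of efficacy. That stands. The fault lies in combining this position with the sizing aim.

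Second, the ten measures are not equal rivals. Target words are called a key outcome, and both the Background and the abstract's Discussion point to word learning. This makes sizing on SRS-2 or VABS-3 unlikely and is why the two-task case is the more realistic one. It does not settle which task or which visit.

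Third, analysis is to be blind to allocation, and data and code will be shared. Both help, but neither stops someone from picking the measure with the largest difference between coded groups, or from choosing after unblinding.

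Fourth, assessing the measures is one of the trial's purposes, so choosing the full trial's primary outcome afterwards on missing data, floor or ceiling effects, or reliability is legitimate. That also stands, and the fix keeps it.

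Some stronger inferences are tempting and unsupported:
- A reader might infer a multiplicity problem with an inflated false-positive rate. The analysis section is descriptive and states no between-arm test and no significance level, so there is no error rate to inflate.
- A reader might multiply measures by visits to reach a much larger number of competing contrasts. That count depends on the schedule figure, which is not available here, and the target-word tasks are not listed at mid-intervention.
- A reader might take the dissemination aim, to "inform clinicians and parents of the potential usefulness or otherwise of the music-assisted programmes", as a planned efficacy claim. The wording is neutral.

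**Conclusion.** The point holds in a limited form. The article declines to rank its outcomes, uses them to size one full trial, and names no outcome or time point for doing so. Following it as written permits sizing on an effect selected for its size. Nothing in it says that the team intends this.

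If it happened, and a true 0.3 SD effect were present, the full trial would be planned with about 73 per arm when choosing between the two target-word tasks, and about 29 per arm in the worst case of the best of ten measures, against about 175 needed. These figures illustrate the mechanism under the stated assumptions on completers, correlation, effect, level and power. They do not predict what this trial will report. The abstract's wording about testing whether MAP increases spoken language goes beyond the objectives and is a secondary matter of consistency.

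**What to change.** 1. In Baseline and outcome measures and in Data handling and analysis plan, name one candidate primary outcome and one time point for sizing the full trial, for example expressive target words at post-intervention.
2. State that the full-trial size will use that outcome's SD, missingness and retention together with a justified target difference, and not the observed difference. Even a pre-named estimate has a half-width of about 0.80 SD at 12 per arm.
3. Allow the candidate to be replaced only for stated feasibility reasons (missing data, floor or ceiling effects, reliability), never because of the observed difference between arms.
4. Describe between-arm outcome comparisons as exploratory, and change the testing language in the abstract's Methods to estimation, in line with the objectives in the Background.

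Dissemination policies needs no change, provided that no efficacy claim is made. The cost is wording only, with no added children, assessments or staff. The small downside is that the team gives up the freedom to choose the sizing outcome after seeing the results.

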
**Fig. 1 Fig1:**
[figure not shown]
Schedule of data collection

### Data handling and analysis plan

All electronic data will be stored in a secure password-protected folder to which only the trial team will have access. Video recordings and questionnaire-based outcome measures will be coded and scored by research assistants who are blinded to the study purpose, treatment allocation, and testing order.

We will record and report the participant flow according to CONSORT guideline and produce a CONSORT flowchart [45, 46]. As a feasibility trial, we will report recruitment and retention figures for both MAP and TAU together with reasons for loss of participants. The trial management will consider any adverse effects and use that information to continue or halt the trial. In addition, we will discontinue the trial at the request of the caregivers, ongoing distress on the part of either the child or the caregiver, and if the caregiver takes up an additional language intervention during the trial. We expect to analyse recruitment and retention data using descriptive statistics involving both intention to treat and actual completed participant data. Recruitment and retention will be encouraged by payment of £202.50 ($283.00) to participants families for completing the research. The amount of the missing data will be recorded in order to assess the feasibility of using each measure. An important part of the feasibility is the extent to which it is possible to conduct two training sessions per week and still maximise the homework practice. We will therefore review the uptake/usage pattern of all MAP parent-child dyads to establish the feasibility of delivering 36 sessions over 18 weeks. For the outcome measures, descriptive data will include means and standard deviations for continuous normal data, and medians and inter-quartile ranges for continuous non-normal or discrete data. Standard errors/confidence intervals will also be calculated for continuous normal data or percentages. Statistical analyses will be performed in R [47]. The results from these analyses will provide data for effect size estimation. Together with the trial parameter data (i.e., recruitment, retention, follow-up and completion rate), these data will be used to determine the size of sample necessary to carry out a fully powered randomised controlled trial comparing MAP with SCIP. A preliminary categorical analysis of words learnt may be used to inform the selection of future vocabulary items for a subsequent trial. The numerical data will be analysed blind to allocation. The blinding will be carried out once the data are collected by generating a new series of participant codes, removing data that could lead to identification (TW) and then be analysed by the PI (FL). Anonymised behavioural data and statistical analysis codes will be made available following open access guidelines. The qualitative interview data will be transcribed and analysed using the thematic analysis framework [48] and Nvivo 12 [49].

If during the course of the trial, we make observations which raise concerns about the children’s wellbeing and safety, we will follow the procedures and policies as outlined by the Keeping Children Safe Standards in the EU [50], the Safeguarding Vulnerable Groups Act 2006 in the UK [51], and the University of Reading DBS policy [52] and safeguarding policy [53] to respond to any safeguarding concerns. There will be no data monitoring committee because the number of participants is small and the primary data offer few opportunities for analysis methods. The trial therapists (MJ and MK) are supervised by TL and [name] as part of the clinic quality control procedures.

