This evidence supports the use of music as a mechanism for intervention and a review of music therapy for individuals with ASD reported that music-based intervention may improve interaction and social communication, including verbal communication [5]. However, the evidence was limited by the small sample sizes of the included studies. More recently, a review of music-based intervention, including for children with ASD, found most studies measured social communication rather than language outcomes [17]. Where language was a target of intervention, evidence was positive but not conclusive. Thus, basic science and evidence from music-based intervention provide a rationale for the aim of this research to use the musical skills and interests of children with ASD to improve learning of single words.

The main objectives of this trial are therefore (1) to determine the feasibility of carrying out a randomised controlled trial of music-assisted programmes delivered remotely due to the COVID-19 pandemic to preschool children with minimal or no spoken language skills, (2) to provide essential parameter data to calculate the sample size and the effect size estimates of a future full-scale trial, (3) to optimise the music-assisted intervention design through a post-intervention interview study with parents, and (4) to pilot and refine an app available on smartphones for supporting and recording homework sessions alongside the intervention.

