## Methods/design

### Study design

The study is a randomised controlled trial comparing speech and language treatment as usual with a music-assisted programme for learning language. The online version of the free open-source Python programme, MinimPy [18], will be used by the PI (FL, who will have no prior interactions with the participants) to assign the participants randomly to either the music-assisted (MAP) intervention or treatment as usual (TAU) group using minimisation randomisation. This method prevents selection bias and minimises the imbalance in prognostic factors of participants between treatment groups [19]. Gender, developmental stage (IQ ≥ 70 or 50–69) and echolalia (present or absent, as reported by the parents) will be used to balance participants between groups.

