### Participants

Thirty children with ASD will be recruited. This sample size was determined partly based on sample sizes of previous studies that used a similar design, ranging from six [20], twelve [21], 23 [22], to 50 divided across three groups (18, 18, 14 in each group) [23]. In addition, for a small randomised controlled feasibility trial like the current one, the sample size can be established according to the precision required for the critical objectives (e.g., estimation of recruitment rate), rather than through power analysis [24]. With a sample size of 30, we will be able to estimate a drop-out rate of 20% to within a 95% confidence interval of +/− 14% [25]. Finally, it has been recommended that pilot studies should include 12 per group [26] or 30 or more participants [27, 28] in order to estimate the means and standard deviations of the outcome measures, as well as to facilitate a sample size calculation for the full trial. Thus, a sample size of 30 is deemed adequate for the current study.

Participants will be screened for autism spectrum disorder using the Social Responsiveness Scale-2 (SRS-2) [29]. They will be between 24 and 60 months old, with little or no spoken language, defined operationally as fewer than 20 functional words [30]. Adapting Dawson et al. (2010: e18) [31], the following will be the exclusion criteria:A neurodevelopmental disorder of known aetiology (e.g., fragile X syndrome);Significant hearing or motor impairment;Major physical problems such as a chronic serious health condition;Seizures at time of entry;History of a serious head injury and/or neurologic disease;IQ below 50 as measured by the Vineland Adaptive Behavior Scales – Third Edition [32]; andNot meeting the cut-off score for ASD on the SRS-2.

The participants will be recruited from special education preschool provision, National Health Service (NHS—state funded), voluntary groups, social media and privately funded clinics in the UK. The parents of potential participants will be approached by letter or email initially and asked to complete an online questionnaire assessing the child’s eligibility and asking for consent to take part in the trial. All data will be held on a secure password-protected database accessible only to the research team.

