### Interventions

To ensure social distancing as required by UK COVID-19 regulations, assessments and interventions will be carried out by the parents under online guidance from the research speech and language therapist using Microsoft Teams. The interventions will consist of 36 training sessions of 45 min duration delivered at the rate of two sessions a week for 18 weeks, during which the parent will be coached by the therapist carrying out a range of activities with the child. In addition, parents will be encouraged to carry out a minimum of five 10-min practice sessions with their children per week. Each week, one such session will be recorded and jointly reviewed by the therapist and the parent to enable better tailoring of the treatment.

The MAP intervention will be as follows (Protocol version MAP-005): (1) Naturalistic strategies will be used, such as incidental learning, high-density repetition, time-delay and mand-modelling. (2) For each of the 36 target words, we will create a set of songs providing the contexts where it occurs. During each session, the songs will be played using a computer or a phone, and sung with a range of home-made music instruments such as shakers. (3) The children will be taught to sing the songs, in which the target words will be occurring repetitively, together with other engaging and interactive activities such as dancing, vocalising, improvising, and playing musical games. (4) Parents will be taught strategies including intensive interaction and communication temptations to help them engage with their children. Parents will also be provided with an app (software programme for Android phones) written to provide the target words songs. The app enables tracking of the amount of practice sessions (i.e., without the therapist present) undertaken by each parent-child dyad.

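### Session uptake and home practice are to be reviewed in the MAP arm only, although both arms are given the same schedule and the next trial is to compare the two

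*Protocol article*

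**What the plan says.** All references are to the protocol article.

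- **Interventions** gives the schedule before it describes the arms separately: "The interventions will consist of 36 training sessions of 45 min duration delivered at the rate of two sessions a week for 18 weeks". For home practice it adds that "parents will be encouraged to carry out a minimum of five 10-min practice sessions with their children per week". One practice session each week is recorded and reviewed jointly by therapist and parent. None of this is limited to one arm, and the TAU description that follows gives no other schedule.
- The MAP part of the same section provides "an app (software programme for Android phones) written to provide the target words songs". The app is said to track practice done without the therapist. No counterpart is described for TAU.
- **Background** lists as the fourth objective "to pilot and refine an app available on smartphones for supporting and recording homework sessions alongside the intervention".
- **Data handling and analysis plan** asks whether two training sessions a week can be combined with as much homework as possible. It answers: "We will therefore review the uptake/usage pattern of all MAP parent-child dyads to establish the feasibility of delivering 36 sessions over 18 weeks". The same section names both MAP and TAU when it plans recruitment and retention figures. It then says that the results will inform effect size estimation and the sample size of a full trial of MAP against SCIP.

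**The concern.** The regimen is common to both arms, but the review of whether families can keep to it is written for one. The section names both arms when it means both, so the natural reading of the sentence is that TAU dyads are left out.

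Two things are at stake. First, the full trial needs to know whether families in either arm can sustain this schedule, and the plan uses only part of the available evidence. Second, the between-arm effect size will be carried forward without a planned account of how much coached time and home practice each arm received. If practice differs between arms, a reader of the feasibility report would not see it. TAU practice that is not counted week by week is hard to recover afterwards.

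**Working it through.** **1. Inputs.** From Participants: "Thirty children with ASD will be recruited", with the size justified partly by the ability to "estimate a drop-out rate of 20% to within a 95% confidence interval" of plus or minus 14 points. From Study design: participants are allocated "to assign the participants randomly to either the music-assisted (MAP) intervention or treatment as usual (TAU) group using minimisation randomisation"; no ratio is given, so 15 per arm is an assumption (1:1). From Interventions: 36 sessions of 45 min, 18 weeks, five practices of 10 min a week.

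**2. The plan's own figure.** Half-width = 1.96 × √(p(1 − p)/n). With p = 0.20 and n = 30: 1.96 × √(0.16/30) = 0.143, or 14.3 points. The stated 14 reproduces. The schedule is also consistent: 36/18 = 2 sessions a week.

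**3. Planned dose per child.**
- Coached: 36 × 45 = 1,620 min = 27 h.
- Home practice, at the stated minimum: 18 × 5 × 10 = 900 min = 15 h.
- Total: 2,520 min = 42 h. Home practice is 15/42 = 36%.

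**4. What the article says is recorded, by component.**

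| Component | Planned hours | MAP | TAU |
|---|---|---|---|
| Coached sessions | 27 | Therapist guides online; uptake review planned | Therapist guides online; no uptake review stated |
| Home practice | 15 | One recorded practice a week; app count (Android); uptake review planned | One recorded practice a week; no total count stated |

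If the recorded practice is one of the five, it accounts for 18 × 10 = 180 min = 3 h. That leaves 15 − 3 = 12 h, or 12/42 = 29% of planned exposure, with no stated record in TAU.

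**5. Effect of using one arm on precision.** The article defines no yes/no adherence rate, so a binomial interval is only illustrative. For a 20% (or 80%) rate on 15 dyads it is 1.96 × √(0.16/15) = 0.202, or 20.2 points, against 14.3 on 30. The ratio does not depend on the binomial form: for a mean number of sessions per dyad with a similar spread in both arms, the standard error is SD/√n, and √(30/15) = 1.41. Intervals from MAP alone are thus about 1.4 times as wide as those from both arms together, given 1:1 allocation.

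**The case against.** There is a fair case for leaving the sentence alone. MAP is the novel intervention, and TAU is modelled on existing clinic practice, so a focus on MAP delivery is defensible. The trial is a feasibility study with descriptive outcome analysis and no primary outcome. The app belongs to the MAP package, so any extra practice it prompts is arguably part of the intervention. The article also cites a protocol version that is not shown, and attendance logs or TAU practice records may be set out there.

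Much of this stands, and it rules out several stronger readings that a reader might infer:

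- *That session uptake is measured through the app.* The review sentence does not mention the app. The app tracks only practice without the therapist, and the therapist is present at the coached sessions whatever phone the family owns.
- *That delivered dose cannot be compared, or that TAU practice is not measured at all.* The therapist coaches the sessions and reviews one recorded practice a week, with no limit to one arm. What is missing is a stated plan to compare, and a stated total count of TAU practice.
- *That a known share of MAP families will have no app record.* The article describes an Android app and, in the objectives, smartphones in general. It gives no figure for families without Android and does not say how they are handled.
- *That the trial fails because it cannot separate music from practice.* Establishing efficacy is not among its objectives.

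The objection does not remove the stated restriction. The sentence does not merely leave TAU unmentioned for a fuller document to cover; it names the dyads to be reviewed, and they are MAP dyads. The focus on a novel arm also sits poorly with the stated use of the data, which is to plan a comparison with SCIP.

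**Conclusion.** The point holds as a fault in what the analysis plan chooses to review. One schedule applies to both arms, the uptake review covers one, and no comparison of delivered dose is planned.

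The review uses about 15 of 30 dyads under an assumed 1:1 allocation, which costs a factor of about 1.4 in precision if uptake varies similarly in the two arms. Home practice, 36% of planned exposure at the stated minimum, has no stated total count in TAU beyond the weekly recording. The conclusion rests on reading MAP in the sentence as the arm label, as it is used elsewhere in that section. It makes no claim about what the full protocol records, about how many families own which phone, or about whether practice will in fact differ between arms. It does not threaten the trial's validity; it is a cheap improvement worth making.

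**What to change.** Rewrite the sentence in Data handling and analysis plan so that session attendance and home practice are reviewed in all dyads of both arms.

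- **Attendance:** take it from therapist session records, in the same form in each arm.
- **Home practice:** use one common weekly entry, the number of practice sessions and the minutes, taken at the joint review of the recorded session that is already planned.
- **Reporting:** give sessions and minutes by arm and overall, with the between-arm difference and its confidence interval. Present the difference as description and as input to the next trial's design, not as a test.
- **App logs:** keep them as a secondary source for MAP families with Android phones, where they can also be checked against the parents' weekly entries.

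The cost is one short question a week at an existing contact. Parent-reported minutes are less exact than app logs, but they come from the same source in both arms, and a comparison between arms needs that.
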